#### Microbiome analysis

To carry out a microbiome analysis, stool samples are collected at baseline and post-intervention. Metagenomic shotgun sequencing enables a taxonomic and functional analysis of the microbiome. Furthermore, the neurotransmitters tyramine, tryptamine, phenylethylamine, dopamine and serotonin are analysed. As a control, stool samples from thirty-two people without obesity and depression will be analysed.

#### Economic evaluation

Food diaries are used to calculate the costs of nutrition before and after the intervention. Using the European Quality of Life 5 Dimensions 5 Level^(49)^ questionnaire, quality-adjusted life years are calculated. These are used to carry out a cost–utility analysis from the participants’ perspective.

#### Qualitative evaluation

In addition to quantitative data, a qualitative evaluation will be conducted. At post-intervention (T1), all participants will be invited to take part in an interview. Interviews will be semi-structured and conducted by study personnel until the results have reached saturation. Interviews will cover two subject areas: (1) the perception of the intervention in terms of feasibility, difficulties in implementation, perception of study setting, planning of long-term implementation, etc., and (2) perception of effects of interventions, qualitative evaluation of changes in outcomes, that is, mood, psychological and physical well-being, self-efficacy, etc. Data analysis will be conducted using MaxQDA Software. The evaluation is based on qualitative content analysis of Mayring^(50)^, in which a defined question is analysed using a summarising analysis technique, the creation of a category system and appropriate coding in order to identify patterns, themes and connections. The analysis will be conducted by two researchers (one senior researcher with extensive experience in qualitative research and one PhD candidate) independently, with categories being discussed until consent is reached.

## Statistical analysis

The statistical analysis will be carried out using the programme R version 4.4.0. As a significance level, p ≤ 0·05 is defined. Data will be analysed as an intention-to-treat analysis. To handle missing data, the ‘missForest’ package in R will be used. This package implements a non-parametric imputation method based on random forests. This approach iteratively imputes missing values using a predictive model that leverages relationships among observed data while accounting for both continuous and categorical variables. Default settings for the algorithm will be used, which automatically selects the optimal number of trees and variables per split to maximise imputation accuracy. The primary outcome parameter is analysed confirmatory using a two-factorial ANCOVA, in which the main outcome parameter is modelled as a function of the two factors – mindful eating (yes/no) and Mediterranean diet (yes/no) – and the respective baseline values (linear covariates). Both main effects of the interventions and interactions are considered. Secondary outcomes will be exploratory (without correction for multiple testing) and analysed using the same models as the primary outcome. To estimate the clinical significance of the results, change scores and effect sizes (Hedges’ g) are calculated for between-group comparisons. The clinical relevance of the results is examined by comparing the number of participants who achieve a clinically relevant improvement of at least 5 points^(51)^ on the BDI-II between the groups at week 12 and week 24 using a logistic regression adjusted for the BDI-II baseline value (random effect). The same model is used to compare the number of patients between the groups who reach remission of depression at week 12 and week 24 (BDI-II < 9).

Mediator and moderator analyses are conducted with the PROCESS Package^(52)^. For the mediator analysis, the indirect effect of an independent variable on a dependent variable via a mediator and its significance are tested using the bootstrap method. Mediation paths can be identified and quantified with consideration of control variables. Concerning moderator analysis, the relationship between the moderator and the independent variable is analysed using product terms in the regression model. Strength and direction are determined using coefficients and statistical significance using the bootstrap method.

For economic evaluation, a cost–cost analysis is carried out to compare food costs in different study arms. Costs will be calculated according to participants’ food diaries. Further, a cost–utility analysis from the participant’s perspective is carried out. Utility is measured in quality-adjusted life years, which are calculated using the European Quality of Life 5 Dimensions 5 Level questionnaire^(49)^. Based on the costs and quality-adjusted life years, the incremental cost ratio is calculated.

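### One missForest fill analysed as if observed shrinks the estimated BDI-II effect and gives confidence intervals that cover too rarely

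*Protocol article*

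**What the plan says.** The Statistical analysis section of the protocol article gives one method for missing values: "To handle missing data, the ‘missForest’ package in R will be used". It describes the mechanism as follows: "This package implements a non-parametric imputation method based on random forests", and "This approach iteratively imputes missing values using a predictive model that leverages relationships among observed data". It also states the tuning and its aim: "Default settings for the algorithm will be used, which automatically selects the optimal number of trees and variables per split to maximise imputation accuracy".

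The analysis set is all randomised participants: "Data will be analysed as an intention-to-treat analysis". The text then goes straight to the confirmatory test: "The primary outcome parameter is analysed confirmatory using a two-factorial ANCOVA", with main effects, interaction and the baseline value. Response (at least 5 points better on the BDI-II) is compared by logistic regression at weeks 12 and 24. For remission (BDI-II below 9): "The same model is used to compare the number of patients between the groups who reach remission of depression". Neither has a missing-data rule of its own.

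The section mentions no random draws, no several completed data sets, no pooling of variances and no sensitivity analysis. The iteration it describes is the repeated cycling of the prediction, which does not produce several imputed data sets. It does not say which variables, including the two treatment factors, enter the imputer. The Sample size calculation section allows for 20 % dropout in 64 participants.

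**The concern.** A forest tuned for accuracy returns something close to a conditional mean. Used as an outcome, that value has no residual scatter and carries no imputation uncertainty, yet the ANCOVA counts it as a full observation.

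With about 51 participants to learn from, the forest also pulls predictions toward the overall mean. This narrows the contrast between factor levels among those imputed. A value pulled toward the mean seldom falls below a low cut-off, so remission is undercounted. Imputation accuracy is therefore the wrong target when the aim is an effect estimate with a valid interval.

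At stake are the estimate and interval from the only confirmatory analysis, and the Hedges' g, response and remission figures taken from the same completed data.

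**Working it through.** **Inputs from the protocol article.** N = 64 (16 per group), 20 % dropout and d = 0.86 (Sample size calculation); two-factor ANCOVA with interaction and baseline, and significance at 0.05 (Statistical analysis); remission below 9 (Secondary outcomes). Expected missing: 0.20 × 64 = 12.8, about 13; observed: 64 − 13 = 51.

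**The plan's own figure.** With f = d/2 = 0.43, a one-degree-of-freedom F test in a four-cell ANCOVA with one covariate needs 45 completers, and 45/0.8 gives 57. The stated 64 is larger and was not reproduced by this route. Nothing below depends on it beyond taking N = 64 as given.

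**Assumptions not in the document.** SD 10; correlation 0.5 between baseline and week-12 BDI-II; dropout completely at random; true remission 10–21 %; forest of 100 trees with √p variables tried per split. Scores are truncated at 0, so the realised effect is about 8.1–8.3 rather than 0.86 × 10 = 8.6. Coverage is counted against the full-data mean.

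**Simulation A** (1,000 runs per scenario).
- Small variable set: true effect about −8.2, estimate −7.45, shrinkage 1 − 7.45/8.2 = 9 %. Model against empirical SE under the null was 1.93 against 2.22 (13 % too small). Type I error was 9.0 % for a main effect and 7.3 % for the interaction.
- 19 variables: estimate −6.93, shrinkage about 16 %. SE was 1.95 against 2.00 and type I error 5.5 %.
- Coverage was about 88 % in both. Observed-data ANCOVA and proper multiple imputation (20 data sets) were unbiased, with type I error of 4–6 %.

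**Simulation B** (coded separately; main effect at d = 0.86).

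| Imputer | Analysis | Mean effect | Mean SE | Coverage | Rejected |
|---|---|---|---|---|---|
| Factors included, 700 runs | filled | −7.04 | 1.90 | 88.0 % | 93.9 % |
| | completers | −8.18 | 2.35 | 95.6 % | 93.0 % |
| | nobody missing | −8.13 | 2.08 | 94.4 % | 96.7 % |
| Factors left out, 500 runs | filled | −6.58 | 1.94 | 85.4 % | 92.8 % |
| | completers | −8.33 | 2.35 | 96.4 % | 92.8 % |
| | nobody missing | −8.34 | 2.09 | 94.8 % | 97.0 % |
| Fully iterated, with week-24 BDI-II and MADRS, 250 runs | filled | −7.14 | 1.93 | 89.6 % | 95.6 % |
| | completers | −8.36 | 2.37 | 94.4 % | 93.2 % |
| | nobody missing | −8.29 | 2.09 | 94.8 % | 97.2 % |

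- Shrinkage: 1 − 7.04/8.13 = 13 %; 1 − 6.58/8.34 = 21 %; 1 − 7.14/8.29 = 14 %.
- Precision: 1.90/2.08 = 0.91 and 1.90/2.35 = 0.81. The filled analysis reports more precision than if nobody had dropped out. Imputed values had about 0.20 of the true variance.
- Type I error: with the factors in the one-pass imputer, null effects were rejected in 5.0–8.0 % of runs, about 6 % on average. In the run that gave 8.0 %, full data gave 6.6 %. With the factors left out, the figures were 4.2 % and 4.6 %. Monte Carlo error at 700 runs is √(0.05 × 0.95/700) = 0.8 points.

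**Remission and response.** Among imputed participants, true remission of 21 % became about 2 % in simulation B and 2–6 % in simulation A. True 10 % became under 0.5 %. True response of 65 % became 73–75 %. Over all 64 the weight is 13/64 = 0.203:
- remission: 0.203 × (21 − 2) = 3.9 points; 0.203 × (21 − 6) = 3.0; 0.203 × (10 − 0.5) = 1.9;
- response: 0.203 × (73 − 65) = 1.6 points; 0.203 × (75 − 65) = 2.0.

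**The case against.** **Is it really a single fill?** The article does not use that term, and repeated runs or sensitivity analyses could stand in an analysis plan that is not shown. However, the article itself fixes the package, its settings and its aim, and moves directly to the confirmatory test. A single fill is an inference, but it is the plain reading and nothing in the text contradicts it.

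**Is a fifth of the primary outcome missing?** The 20 % is a planning allowance. The BDI-II is a self-report form that can be completed digitally (Primary outcome; Data management), so leaving the intervention need not mean losing the score. This stands. All sizes here are conditional on about 13 missing scores and fall with fewer.

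**Are standard errors always too small and false positives clearly inflated?** A reader might infer this from a fill that ignores uncertainty. The evidence does not support it in general. Against the estimator's own spread, the shortfall runs from slight (1.95 against 2.00) to 13 %, because shrinkage also narrows that spread. The 9.0 % arises only with a small variable set. The trial collects many measures and does not say which ones enter the imputer, so that set cannot be taken as the plan.

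**Does shrinkage cost power?** A reader might infer this too. In simulation B the filled analysis rejected about as often as completers (93.9 % against 93.0 %). The damage is to the estimate and its interval.

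**Are the trial's remission counts badly wrong?** Only imputed participants are affected. Remission is a secondary outcome, analysed as exploratory, and the shift over all 64 is a few points.

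**Conclusion.** The point holds as a defect in a stated method: a predictor chosen for accuracy is used, on the plain reading, as a single imputation for a confirmatory test. Both simulations agree on three consequences:
- an effect of d = 0.86 is shrunk by about 9–21 %, depending on the imputer's variables;
- 95 % intervals cover about 85–90 % of the time;
- remission is undercounted among those imputed.

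Shrinkage arises only where there is a real effect. Type I inflation is modest (about 5–9 %) and should not carry the argument.

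The sizes rest on about 13 of 64 scores missing completely at random, SD 10, correlation 0.5, true remission of 10–21 % and the assumed forest settings. No range over SD, correlation or dropout mechanism was run, so the percentages are illustrative. The direction of the three main consequences was the same in every setting tried.

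**What to change.** In the Statistical analysis section, replace the single missForest fill in the efficacy analyses with multiple imputation using random draws, for example 20–50 data sets. The imputation model should hold both factors, their interaction, baseline BDI-II and the T1 and T2 BDI-II values. Run the planned ANCOVA in each data set and pool by Rubin's rules. Derive response and remission within each data set before pooling. Delete the sentence on maximising imputation accuracy.

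The planned ANCOVA can stay; the defect does not require a different primary model. ANCOVA on observed data or a likelihood-based mixed model is an acceptable alternative or sensitivity analysis, and missForest may remain as a sensitivity analysis.

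The cost is revised wording and a little more analysis work, with no new data. Reported standard errors will be larger, by up to about 24 % in the simulation (2.35/1.90 = 1.24), because imputed values no longer count as observed.

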## Randomisation

After inclusion, participants are randomised to one of the four intervention groups. Randomisation is performed using a randomisation list with varying block lengths (4, 8, 12) created by the programme R. Group allocation is carried out by members of the research staff via RedCap. Therefore, allocation concealment is given. Severity of obesity (obesity grade 1: BMI 30–35 kg/m^2^; obesity grade 2–4: BMI ≥ 35 kg/m^2^) and severity of depression (moderate depression: BDI-II 20–28; severe depression: BDI-II ≥ 29) are defined as strata. Participants are assigned to one of the four intervention groups in a 1:1:1:1 ratio. Participants will be informed about the group assignment at their first intervention appointment.

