## Sample size calculation

Sample size calculation was carried out with the programme R Version 4.4.0, package ‘pwrss’ version 0.3.1. It is based on effect sizes of comparable interventions of the Mediterranean diet^(32)^ and mindful eating^(33)^ on the primary outcome of the study (BDI-II score). Using a conservative approach, we have used the lower effect size of d = 0·86 of the mindfulness intervention (Mediterranean diet: d = 1·7) to compute the required sample size. Considering a statistical power of *β* = 0·8 and *α* = 0·05, as well as a 20 % dropout rate for ANCOVA with main and interaction effects and baseline scores as covariate, *n* 64 subjects need to be recruited, that is, sixteen participants in each group.

For microbiome analysis, samples of *n* 32 healthy controls will additionally be analysed, representing the same number of participants receiving each intervention.

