### Primary outcome

As a primary outcome, depression severity is assessed using the BDI-II. This self-report questionnaire records the occurrence of various depressive symptoms in twenty-one questions on a 4-point scale. The BDI-II score ranges from 0 to 63, with higher scores indicating higher depression severity^(40)^.

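### Obesity grade stratifies the randomisation but has no term in the primary ANCOVA, and secondary models that adjust only for their own baseline omit both strata (minor efficiency point)

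*Protocol article*

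**What the plan says.** The Randomisation section sets two stratification factors. The first is "Severity of obesity (obesity grade 1: BMI 30–35 kg/m^2^; obesity grade 2–4: BMI ≥ 35 kg/m^2"); the second is "severity of depression (moderate depression: BDI-II 20–28; severe depression: BDI-II ≥ 29) are defined as strata". Allocation is 1:1:1:1 in blocks of 4, 8 or 12.

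Under Primary outcome: "As a primary outcome, depression severity is assessed using the BDI-II". The Statistical analysis section then names the terms of the confirmatory model: mindful eating, Mediterranean diet, their interaction "and the respective baseline values (linear covariates". The sample size section plans for the same model, an "ANCOVA with main and interaction effects and baseline scores as covariate". Secondary outcomes are exploratory and are "analysed using the same models as the primary outcome". The BDI-II response and remission models are logistic regressions adjusted for baseline BDI-II. BMI and obesity grade are named as covariates in none of these places.

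**The concern.** Blocking within strata reduces the true sampling variance of the treatment estimate when the strata predict the outcome. A model without the stratum leaves that variation in its residual. The reported standard error is then larger than the true one, the test rejects below its nominal level under the null, and some power is lost. With 64 people in four strata (64 / 4 = 16 on average) and blocks of up to 12, incomplete blocks are also likely, and the model leaves any resulting imbalance in obesity grade unadjusted.

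This is not a detail left to an unseen analysis plan. The article lists the model's terms in two sections that agree with each other, and the obesity stratum is in neither.

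**Working it through.** **1. Which strata are covered by which model**

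| Model | Depression severity | Obesity grade |
|---|---|---|
| Primary BDI-II ANCOVA | yes, linear baseline BDI-II | no |
| BDI-II response and remission | yes, baseline BDI-II | no |
| MADRS, SF-36, self-efficacy | no | no |
| Waist:hip ratio, body composition | no | not as such (own baseline only) |
| BMI | no | yes, baseline BMI |

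**2. The plan's own sample size.** Inputs: "we have used the lower effect size of d = 0·86 of the mindfulness intervention", so f = 0.86 / 2 = 0.43; α = 0.05; power 0.80; dropout 20 %; one covariate. With noncentrality N·f² and 1 and N − 5 degrees of freedom, a main effect needs 45 analysed, or 48 in equal cells. That is 45 / 0.8 = 56.25, rounded up to 57, or 48 / 0.8 = 60 recruited. The stated 64 is therefore not reproduced for a main effect, but it exceeds what is needed. That is a separate matter. For this point, 64 × 0.8 = 51.2, so about 51 are analysed and main-effect power with baseline BDI-II alone is 85.2 %.

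**3. Closed form for the missing obesity term.** Let R² be the share of residual variance that obesity grade explains given baseline BDI-II. The article gives no value, so 0 to 10 % is an assumption.

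- SE inflation = 1/√(1 − R²) − 1
- Type I error = 2·[1 − Φ(1.96/√(1 − R²))]
- Adjusted power: noncentral F with N = 51, f² = 0.43²/(1 − R²) = 0.1849/(1 − R²), and 45 error degrees of freedom

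| Assumed R² | SE too wide by | Type I error | Power, not adjusted → adjusted |
|---|---|---|---|
| 0 | 0 % | 5.0 % | 85.2 → 85.2 % |
| 2 % | 1.0 % | 4.8 % | 85.2 → 85.9 % |
| 5 % | 2.6 % | 4.4 % | 85.2 → 86.9 % |
| 10 % | 5.4 % | 3.9 % | 85.2 → 88.6 % |

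These formulas treat the stratum as perfectly balanced, and incomplete blocks and dropout prevent that.

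**4. Simulation of the design** (64 randomised, blocks of 4/8/12 in four strata, about 51 analysed, d = 0.86). Ranges are across separate simulations.

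| Assumed R² | Type I error without the term | Power gain from adding it |
|---|---|---|
| 0 | about 4.9 % | about 0 (−0.3 in one run) |
| 2 % | 4.6 to 4.7 % | 0.2 to 0.4 points |
| 5 % | 4.5 to 4.9 % | 1.1 to 1.3 points |
| 10 % | 3.9 to 4.3 % | 2.3 to 2.8 points |

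At R² = 5 % the average standard error was 0.283 without the term and 0.277 with it (0.283 / 0.277 = 1.022, so 2.2 % wider). The direction agrees with the closed form, but the power gains are smaller than its 0.7, 1.7 and 3.4 points.

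**5. The depression stratum in the primary model.** In a simulation with 64 randomised, 20 % dropout and an assumed baseline–outcome correlation of 0.5, the standard error was 0.288 with no baseline covariate and 0.2444 with linear baseline BDI-II. Adding the two-level severity stratum on top gave 0.2464, about 0.8 % wider (0.2464 / 0.2444 = 1.008), with no gain in power. Linear baseline BDI-II already captures that stratum.

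**The case against.** A reader who sets "severe depression: BDI-II ≥ 29) are defined as strata" beside the ANCOVA might infer that the primary model ignores both stratification factors. The documents do not support this. The depression stratum is a cut of baseline BDI-II, and baseline BDI-II is the linear covariate, which holds more information than the two-level version. In the same way, the BMI model already carries baseline BMI and needs no obesity term.

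The remaining loss depends on an R² that the article does not give, and zero is possible. The Introduction reports that the obesity–depression correlation strengthens with higher BMI. It does not say that BMI above or below 35 predicts 12-week BDI-II given baseline BDI-II among people who all have BMI of at least 30. The two halves of the argument also offset each other: the more chance imbalance there is, the less conservative the unadjusted test.

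Finally, main-effect power at 51 analysed is above the 80 % target without the extra term, any error is on the conservative side, and the secondary outcomes are declared exploratory. All of this stands, and it limits the point to a minor one. It does not remove the mismatch: the sponsor thought obesity grade important enough to balance, then left it out of the confirmatory model.

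**Conclusion.** The point holds as a minor matter of efficiency and consistency. Obesity grade is absent from the primary model and from the response and remission models. Secondary models with only their own baseline, such as MADRS, SF-36 and self-efficacy, lack both strata.

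The size rests on an assumed partial R² of 0 to 10 %, about 51 analysed and d = 0.86: standard errors about 0 to 5 % too wide, type I error going from about 5 % down to about 4 %, and 0 to about 3 points of power to be gained. If the true effect were smaller, say 0.6 (an assumption), the closed form moves power from 55.5 % to 57.6 % at R² = 5 % and to 59.9 % at 10 %, still only a few points.

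It would be wrong to infer that the primary test is biased or invalid, or that power is certainly lost. The omission is conservative where it matters at all, and nothing is lost if obesity grade is not prognostic.

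**What to change.** Before unblinding, add a sentence to the Statistical analysis section that does the following:

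- Include obesity grade as randomised (or baseline BMI) as a fixed covariate in the primary BDI-II ANCOVA, in the response and remission models, and in every secondary model that does not already contain baseline BMI.
- Include baseline BDI-II in the secondary models where it is absent. The two-level severity stratum need not be added where linear baseline BDI-II is already present.

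The cost is one degree of freedom in the primary model and one or two in the secondary models. At R² = 0 the closed form puts the loss at 0.03 points of power (85.23 % to 85.19 %), and the simulations at no more than about 0.3 points. In the logistic models the odds ratio becomes conditional on obesity grade as well as baseline BDI-II, which the report should state. The data are already collected. Making the change now avoids the appearance of a covariate chosen after seeing the results.

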### Secondary outcomes

#### Remission

Remission rates will be assessed as the number of patients who no longer show depressive symptoms, defined as BDI-II < 9.

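### The logistic models for 5-point response and remission enter baseline BDI-II as a random effect where a fixed linear covariate is needed (minor correction to secondary analyses)

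*Protocol article*

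**What the plan says.** All statements are in the protocol article; no separate SAP was available.

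- **Responder model (Statistical analysis).** The endpoint is "a clinically relevant improvement of at least 5 points" on the BDI-II at weeks 12 and 24. Groups are compared "using a logistic regression adjusted for the BDI-II baseline value (random effect" (the bracket closes there).
- **Remission model (Statistical analysis).** "The same model is used to compare the number of patients between the groups who reach remission of depression at week 12 and week 24". The Remission section lists this as a secondary outcome, "defined as BDI-II < 9".
- **Primary model (Statistical analysis).** The two-factor ANCOVA uses the two interventions "and the respective baseline values (linear covariates", with main effects and interaction.
- **Secondary outcomes (Statistical analysis).** They are exploratory, without multiplicity correction, and "analysed using the same models as the primary outcome".
- **The baseline variable (Primary outcome).** "The BDI-II score ranges from 0 to 63". The inclusion criteria require at least 20.

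**The concern.** A random effect needs a grouping unit whose members share something unobserved, such as a site, a therapist or a participant measured repeatedly. A baseline depression score is none of these. It is a measured, ordered, prognostic quantity, and what adjustment should use is its gradient: a participant entering at 20 is closer to remission than one entering at 45. The trial has one centre and the appointments are one-on-one, and the article names no other unit to which the label could refer.

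The section also gives the same variable two incompatible roles, linear covariate in one model and random effect in another, without a reason. At stake is whether the analyses of clinical relevance and remission are really adjusted for baseline, as the plan says they are. A secondary question is whether the analyst is left to choose the model after seeing the data.

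**Working it through.** **No stated figure to reproduce.** The plan gives no power, event rate or sample size for these two models, so the check concerns the specification. Every simulation input not attributed to the protocol below is an assumption.

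**1. The two models.** Let MD and ME be the factors and B the baseline score.

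- Linear covariate: logit P(Y=1) = α + β₁MD + β₂ME + β₃MD·ME + γB.
- Literal reading: logit P(Y=1) = α + β₁MD + β₂ME + β₃MD·ME + u_B, with u_B ~ N(0, τ²) and one draw per distinct score.

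In the second model u₂₀, u₂₁ and u₅₀ are independent, so 20 is no more like 21 than like 50. If τ² is estimated as zero, every u is zero and baseline drops out.

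**2. Cluster size.** Possible entry scores run from 20 to 63, which is 63 − 20 + 1 = 44 values. With N = 64 (Sample size calculation) and an assumed baseline mean of 28 to 32 and SD of 7 to 9, about 21 to 26 distinct scores occur. That is 64/26 = 2.5 to 64/21 = 3.0 people per score, very little from which to estimate a between-score variance.

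**3. How often the variance collapses to zero.**

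| Assumed inputs | Share of runs with zero variance |
|---|---|
| N = 64; effect 8.6 points (the protocol's d = 0.86 × assumed SD 10); correlation 0.5; 400 runs | 34 % (remission), 59 % (response) |
| N = 64 or 52; baseline mean 30, SD 8, limited to 20–55; slope 0.6; residual SD 8; 5 points per factor; control follow-up mean 20 or 26; 300 runs per scenario | 42–60 % |
| N = 64; baseline mean 30, SD 8 | 41–59 % |

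**4. How much adjustment is left.** These results use the inputs in the second row.

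- The SD of baseline's contribution to the log-odds (median per scenario) was 0.58 to 1.14 as a linear covariate and 0.00 to 0.11 as a random effect.
- Where the variance was above zero, the predicted score effects correlated only 0.28 to 0.42 with the score itself.
- The mean absolute distance of the treatment log odds ratio from the linear-covariate estimate was 0.16 to 0.29 with the random effect and 0.14 to 0.26 with no baseline term. On this measure the random effect was no better than leaving baseline out.

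Runs with fewer than four events or non-events, or with extreme estimates, were dropped, leaving 107 to 300 of 300 per scenario. The percentages are therefore indicative.

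**5. Cost in power.** Complete loss of adjustment is the natural benchmark. Dropping baseline altogether, compared with the linear covariate, cost:

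- about 2 to 7 points for remission and 0 to 3 for response (baseline mean 28–32, SD 7–9, effect 8.6, SD 10, correlation 0.5, control improvement 4–12 points; 1,000 runs per setting);
- about 4 to 6 points and 0 to 2 points respectively with baseline mean 30 and SD 8.

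The 400-run simulation in the first row compared the random effect with the linear covariate directly. It gave 47 % against 58 % for remission and 55 % against 57 % for response. The Monte Carlo standard error of each estimate is about √(0.5 × 0.5/400) = 2.5 points.

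**6. Why remission is affected more.** Remission means a score of 8 or less. From 20 that is a fall of at least 20 − 8 = 12 points; from 29, the lower bound of the severe stratum, at least 29 − 8 = 21. The 5-point response asks for the same fall from every starting score.

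**The case against.** The best defence is that the bracket is a slip. The sentence names a logistic regression adjusted for baseline and mentions no mixed model and no intercept per score; the words may have been meant as fixed effect, or as a participant effect across the two weeks. That is plausible, and it cannot be shown that anyone will fit score-level clusters. It does not rescue the text, because the possible intentions lead to different models and the article does not say which applies.

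Three further points on that side stand:

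- These analyses are exploratory or supportive, and the primary ANCOVA already handles baseline correctly.
- Randomisation is stratified by BDI-II (20–28 against 29 or more), so baseline is partly balanced by design. The consequence is lost precision, not a biased group comparison.
- The loss is partial: in the first-row simulation 66 % of remission fits did not have zero variance.

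A reader might be tempted by stronger readings that the document does not support:

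- **An 11-point power loss for remission (58 % against 47 %).** This exceeds the 2 to 7 points found when adjustment was removed entirely. It depends on an unstated control-group improvement and comes from a model without the planned interaction. For the 5-point response, the 2-point difference is within simulation error.
- **A missing repeated-measures term.** Comparing groups at week 12 and week 24 reads naturally as two separate analyses, which need no participant effect.
- **Too few events among about 51 completers, calling for penalised likelihood.** The plan specifies intention-to-treat with imputation, so 64 are analysed, and the document gives no remission rate. Penalisation is an optional refinement unrelated to this error.

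**Conclusion.** The specification is wrong as written, and nothing elsewhere in the article corrects it. Taken literally, it replaces a one-parameter gradient with 21 to 26 unordered clusters, and in roughly 35 to 60 % of simulated trials it reduces to an unadjusted model. The practical cost is a few points of power for remission and next to nothing for the 5-point response. These sizes rest on assumed baseline distributions, correlations, effects and control-group courses, none of which the protocol supplies for these endpoints; the misclassification of the covariate does not depend on them. This is a minor correction to a listed secondary outcome and a supportive analysis. It gives no ground for doubting the confirmatory test.

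**What to change.** Delete the random-effect label and state that, for both the 5-point response and remission, a logistic regression is fitted separately at week 12 and at week 24 with Mediterranean diet, mindful eating, their interaction, and baseline BDI-II as a fixed linear covariate. This matches the structure of the primary ANCOVA. If the intention is to model both weeks jointly, say so and place a random intercept on participant, still keeping baseline BDI-II as a fixed covariate.

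The cost is one sentence, settled before the data are analysed. It requires no change to data collection, sample size or the primary analysis.
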